# A phase III, multicenter, randomized controlled trial of preoperative versus postoperative stereotactic radiosurgery for patients with surgically resectable brain metastases

**DOI:** 10.1186/s12885-022-10480-z

**Published:** 2022-12-30

**Keywords:** Brain metastases, Stereotactic radiosurgery, Preoperative, Postoperative, Quality of life, Neurocognitive outcomes

## Abstract

**Background:**

Postoperative stereotactic radiosurgery (SRS) is a standard management option for patients with resected brain metastases. Preoperative SRS may have certain advantages compared to postoperative SRS, including less uncertainty in delineation of the intact tumor compared to the postoperative resection cavity, reduced rate of leptomeningeal dissemination postoperatively, and a lower risk of radiation necrosis. The recently published ASCO-SNO-ASTRO consensus statement provides no recommendation for the preferred sequencing of radiotherapy and surgery for patients receiving both treatments for their brain metastases.

**Methods:**

This multicenter, randomized controlled trial aims to recruit 88 patients with resectable brain metastases over an estimated three-year period. Patients with ten or fewer brain metastases with at least one resectable, fulfilling inclusion criteria will be randomized to postoperative SRS (standard arm) or preoperative SRS (investigational arm) in a 1:1 ratio. Randomization will be stratified by age (< 60 versus ≥60 years), histology (melanoma/renal cell carcinoma/sarcoma versus other), and number of metastases (one versus 2–10). In the standard arm, postoperative SRS will be delivered within 3 weeks of surgery, and all unresected metastases will receive primary SRS. In the investigational arm, enrolled patients will receive SRS of all brain metastases followed by surgery of resectable metastases within one week of SRS. In either arm, single fraction or hypofractionated SRS in three or five fractions is permitted. The primary endpoint is to assess local control at 12 months in both arms. Secondary endpoints include local control at other time points, regional/distant brain recurrence rates, leptomeningeal recurrence rates, overall survival, neurocognitive outcomes, and adverse radiation events including radiation necrosis rates in both arms.

**Discussion:**

This trial addresses the unanswered question of the optimal sequencing of surgery and SRS in the management of patients with resectable brain metastases. No randomized data comparing preoperative and postoperative SRS for patients with brain metastases has been published to date.

**Trial registration:**

Clinicaltrials.gov, NCT04474925; registered on July 17, 2020. Protocol version 1.0 (January 31, 2020). Sponsor: Alberta Health Services, Edmonton, Canada ([name]).

## Background

Brain metastases occur in 10–30% of cancer patients and can lead to devastating neurological deficits and neurocognitive decline that can significantly affect quality-of-life [1–3]. Surgical resection of intracranial metastases can be indicated for patients with larger tumors (> 2 cm in diameter), symptomatic lesions, or need for tissue for diagnosis or clinical trial enrollment [4]. Postoperative whole brain radiotherapy (WBRT) has been shown to improve local control and reduce neurological death rate after intracranial tumor resection [5, 6]. Concerns about neurocognitive decline resulting from WBRT led to a multicenter randomized phase III trial by Brown et al. comparing postoperative WBRT with stereotactic radiosurgery (SRS) in 194 patients. With a median follow up of 11.1 months, cognitive function and quality of life were better in SRS arm without any significant difference in overall survival [7]. Postoperative SRS is now considered a standard of care option for patients in addition to WBRT.

Treatment planning tends to be more complicated with postoperative SRS than in the preoperative setting, and this factor has been suggested to contribute to the higher local failure rate seen in the SRS arm compared to WBRT in trial by Brown et al. [7]. Further, leptomeningeal disease (LMD) has frequently been reported in case series of postoperative SRS [8–13]. Preoperative SRS has been suggested to help ease target delineation to simplify treatment planning, reduce the planning target volume (PTV) margin to reduce the treatment volume, shorten the overall treatment time, and reduce the risk of leptomeningeal dissemination after surgery [14].

Patel et al. published findings from a multi-institutional retrospective study comparing preoperative and postoperative SRS in 180 patients [15]. The median follow-up period was 24.6 months, and 36.7% of all patients received preoperative SRS. There was no significant difference between the two groups in terms of local recurrence, overall survival, and distant brain recurrence. However, postoperative SRS was associated with higher rates of leptomeningeal recurrence and symptomatic radiation necrosis (SRN). The SRN rate was higher in postoperative patients (16.4%) compared to preoperative patients (4.8%) at two years. The LMD rate was 16.6% in postoperative patients compared to 3.2% of preoperative patients (*p* = 0.010). The authors suggested that sterilization of the treatment field by preoperative SRS may restrict tumor cell dissemination during surgery to account for the lower rate of LMD with preoperative SRS. The PROPS-BM multicenter, retrospective study included 242 patients treated with preoperative SRS [16]. The 2-year rates of LMD and ARE were low at 7.6 and 6.8%, respectively. On multivariate analysis subtotal resection (STR) resulted in worsened local control and overall survival (OS). The authors suggest that a fractionated regimen of radiosurgery for patients at high risk of subtotal resection to increase the biological effective dose delivered to the target volume, consistent with previous literature in patients treated with postoperative SRS [17].

A potential rational for lower SRN in patients treated with preoperative SRS that normal tissue surrounding the SRS target receiving high doses of radiation will subsequently resected thereby decreasing the available injured tissue and cytokine concentration which might augment a radiation necrosis reaction [18, 19]. A contributing factor is that studies of preoperative SRS have used smaller PTV margins, typically 0–1 mm, compared to trials of postoperative SRS (e.g., 2 mm in the NCCTG N107C/CEC.3 trial) [7]. Postoperative contouring guidelines recommend an additional margin of 5–10 mm along the dura if dural contact was observed on preoperative imaging [20]. These rationales are supported by dosimetric data reported by El Sahfie et al. that show reduction in the dose exposure of the normal healthy brain with preoperative versus postoperative SRS [21]. The median volume of healthy brain receiving 28 Gy was 6.79 cc with preoperative SRS compared to 10.79 cc with postoperative SRS (*p* < 0.001).

The ASCO-SNO-ASTRO consensus statement for the treatment of brain metastases with radiosurgery indicates that there is no recommendation regarding the sequencing of surgery and SRS [22]. There are no randomized data comparing preoperative and postoperative SRS currently in the literature [23]. The present study is a prospective, multicenter, randomized, controlled trial comparing preoperative to postoperative SRS in the treatment of resectable brain metastases. Importantly, fractionated SRS for both preoperative and postoperative cases, depending on their size, is allowed in this study. The primary objective of the study is to compare the local control of pre- versus postoperative SRS. Secondary objectives are to compare distant brain recurrence, leptomeningeal recurrence, and overall survival of the two arms as well as the comparison of quality-of-life and neurocognitive outcomes of preoperative versus postoperative SRS (Table 1).

**Table 1 Tab1:** Study endpoints

**1.0 Primary endpoints** 1.1 Local control at 12 months.	
**2.0 Secondary endpoints** 2.1 Local control at 6 and 24 months 2.2 Distance brain recurrence rate (%) at 6,12, and 24 months 2.3 Leptomeningeal recurrence rate (%) at 6, 12, 24 months 2.4 Overall survival (in months) at 6, 12 and 24 months 2.5 Hopkins Verbal Learning Test Revised score (points) at 3, 6, 9, 12, 16, 24 months 2.6 Controlled Oral Word Association test score (points) at 3, 6, 9, 12, 16, 24 months 2.7 Trail Making Test score (points) at 3, 6, 9, 12, 16, 24 months	

## Methods

### Study design

This phase III, multicenter, randomized controlled trial will enroll patients brain metastases, of which at least one is resectable. Patients will be randomly assigned to either postoperative SRS (standard arm) or preoperative SRS (investigational arm) in a 1:1 ratio. The study schema is illustrated in Fig. 1.

**Fig. 1 Fig1:**
[figure not shown]
Study schema

### Patient selection and eligibility criteria

Patients with between one and ten brain metastases on contrast-enhanced MRI of the brain will be screened for the study. At least one brain metastases should be deemed surgically resectable after image review or consultation with a neurosurgeon. Further patient eligibility criteria are listed in Table 2. If the patient is eligible for enrolment, a detailed discussion of the study including purpose and potential risks will take place with interested patients. The signed, written, informed consent will be obtained from every patient before trial enrollment.

**Table 2 Tab2:** Patient eligibility criteria

**1.0 Inclusion criteria**	**2.0 Exclusion criteria**
1.1 Age ≥ 18 years 1.2 Pathologically proven primary malignancy 1.3 ECOG performance score of 0–2 1.4 MRI with contrast demonstrating ten or fewer brain metastases, of which at least one is resectable as deemed by a neurosurgeon 1.5 Ability to complete neurocognitive testing without assistance from family or friends. 1.6 Previous SRS to lesions other than the one being resected is allowed 1.7 Patients with childbearing potential must have a negative urine or serum pregnancy test ≤7 days before enrolment 1.8 Participants capable of giving informed consent, or if appropriate participants having an acceptable individual capable of giving consent	2.1 Patients who have received prior WBRT, or SRS to the lesion being resected at time of study accrual 2.2 Patients unable to undergo MRI scan (e.g., pacemaker) 2.3 Leptomeningeal disease 2.4 Germ cell tumor, small cell lung cancer or hematological primary malignancy

*Abbreviations ECOG* Eastern Cooperative Oncology Group, *SRS* stereotactic radiosurgery, *WBRT* whole brain radiotherapy

### Randomization and treatment allocation

Patients will be allocated by blocked randomization (block size of 16), on a 1:1 basis, to either the standard or investigational arm. Patients will be stratified according to the following factors: age (< 60 years versus ≥60 years), histology (melanoma/renal cell carcinoma/sarcoma versus other) and number of metastases (1 versus 2–10). A computer-generated list has been uploaded into the Electronic Data Capture (EDC) system for randomization. After confirming a participant’s eligibility, the study staff will randomize the patient using the EDC. Following randomization, treatment will be initiated within two weeks. Because of the difference in treatment sequencing (before or after surgery), blinding of trial participants or investigators will not be possible; neuropathologists and neuroradiologists will prospectively review applicable material without knowledge of the random assignment.

### Pre-treatment evaluation

The screening assessments will be done within one week of randomization, performed after having received the participant’s written informed consent. These will include their medical history and demographics, physical examination, Karnofsky performance status, adverse event review, steroid dose assessment, pregnancy testing (for females with childbearing potential), diagnostic MRI scan (within 30 days of randomization), quality-of-life questionnaires and neurocognitive testing. The assessments performed prior to consent as per standard institutional guidelines do not need to be repeated if they fall within the 7-day screening window.

### Interventions

The following procedures will be performed during the treatment phase of the trial:Standard arm: Resection of ≥1 brain metastases followed by postoperative tumor bed SRS within 3 weeks.Investigational arm: Preoperative SRS followed by resection of ≥1 brain metastases within 1 week.

Patients treated on both arms will receive primary SRS for unresected brain metastases.

### Radiotherapy

A linear accelerator (LINAC) using ≥4 megavoltage (MV) photons, with collimation using micro-multi-leaf collimators (5 mm width or less at isocenter) or cones, Gamma Knife or Cyberknife may be used to deliver SRS. All patients will be counselled about thermoplastic mask fixation, CT simulation and immobilization in detail. Localization, simulation, and immobilization will be as per institution standard.

For the tumor bed (standard arm only), the gross tumor volume (GTV) will consist of the tumor bed including residual tumor, if present, on T1-weighted MRI (with gadolinium contrast, unless contraindicated) or CT scan (with contrast, unless contraindicated). The clinical target volume (CTV) will be GTV plus 2 mm and can be cropped for natural barriers to spread (e.g., bone) or structures not at-risk for tumor infiltration. The planning target volume (PTV) will be the CTV plus 0 to 1 mm when using mask-based immobilization (no margin will be added when using frame-based immobilization). For intact metastases on both arms, the GTV will consist of all visible tumor on T1-weighted MRI or CT scan. No margin will be added for CTV. The PTV will be the CTV plus 1 mm when using mask-based immobilization (no margin will be added when using frame-based immobilization). Radiosurgery dose and fractionation is based on the NCCTG N107C/CEC.3 trial [7] with modification (Table 3). Treatment will be delivered on consecutive days, one fraction per day, for fractionated radiotherapy regimens.

**Table 3 Tab3:** Radiotherapy dose and fractionation

Tumor Bed (standard arm) (prescription is based on CTV volume)	Intact metastases (both arms) (prescription is based on the CTV maximal diameter)
Lesions < 4.2 cc receive 20 Gy	Lesions < 1.0 cm receive 22–24 Gy
Lesions ≥4.2 to < 14.4 cc receive 17 Gy	Lesions ≥1.0 to < 2.0 cm receive 20–22 Gy
Lesions ≥14.4 to < 30 cc receive 27 Gy in three or 30 Gy in 5 fractions	Lesions ≥2.0 to < 3.0 cm receive 18–20 Gy
Lesions ≥30 cc receive 24–27 Gy in 3 fractions or 30 Gy in five fractions	Lesions ≥3.0 to < 5.0 cm receive 27 Gy in 3 or 30 Gy in five fractions
	Lesions ≥5.0 cm receive 24–27 Gy in three fractions or 30 Gy in five fractions

The dose should be prescribed to the highest isodose line encompassing the CTV and be between the 50 and 90% of the maximum dose

*Abbreviation*: *CTV* clinical target volume

Critical organs at risk (OAR) include the optic nerves and optic chiasm. A margin of 1 mm when using mask-based immobilization (no margin when using frame-based immobilization) will be added to each OAR to create each planning OAR volume (PRV). The dose constraints for the optic nerve and chiasm PRVs are Dmax ≤10 Gy in one fraction, ≤20 Gy in three fractions, and ≤ 25 Gy in five fractions; and for Brainstem are Dmax ≤15 Gy in one fraction, ≤23.1 Gy in three fractions, and ≤ 31 Gy in five fractions.

Multiple isocenter, non-isocentric, and non-coplanar beams may be used. Few parameters to be followed while planning and plan evaluation: 95% of the prescribed dose should completely encompass the target (CTV). Dose conformity (for CTV) should be between 1.0 and 2.0 for lesions ≥5 mm in maximum diameter (may be up to 3.0 for lesions < 5 mm in maximum diameter). The minimum and maximum CTV dose, conformity index (defined as the ratio of the prescription isodose volume to the target volume, i.e., CTV), prescription isodose line, maximum point dose to the optic nerves and chiasm, and dose received by 1 cc of the brainstem should be calculated and reported. The isodose distribution for each plan should be submitted in DICOM-RT format. Total PTV volume, normal brain (brain-GTV) volume receiving 12 Gy (V_12 Gy_) will also be recorded.

Patients may receive other medications/treatments as required. Only steroid therapy will be recorded in the case report forms. Cytotoxic chemotherapy should be stopped during SRS. Immunotherapy may be continued during SRS.

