### Radiotherapy quality assurance

Efforts will be made to keep treatment interruptions to a minimum when feasible. Treatment interruptions are allowed when clinically required at the discretion of the treating physician, for example to allow for patient recovery after resection or between fractions of fractionated SRS or based on available treatment days given holiday schedules. Radiotherapy compliance criteria are listed in Table 4.

**Table 4 Tab4:** Radiotherapy compliance criteria

**1.0 Minor deviations**	1.1 < 95% but ≥90% of the prescribed dose completely encompasses the clinical target volume 1.2 > 3 weeks between resection and start of post-operative SRS in the standard arm 1.3 > 1 week between the end of pre-operative SRS and resection in the experimental arm
**2.0 Major deviations**	2.1 > 2 weeks between planning MRI and start of SRS 2.2 Prescribed dose is ≤90% dose required by the study 2.3 < 90% of the prescribed dose completely encompasses the clinical target volume 2.4 Maximum point dose to the optic chiasm is > 10 Gy for treatments delivered in one fraction, > 20 Gy for treatments delivered in three fractions, or > 25 Gy for treatments delivered in five fractions 2.5 Maximum point dose to the brainstem is > 15 Gy for treatments delivered in one fraction, > 3.1 Gy for treatments delivered in three fractions, or > 31 Gy for treatments delivered in five fractions 2.6 > 6 weeks between resection and start of post-operative SRS in the standard arm or > 3 weeks between the end of pre-operative SRS and resection in the experimental arm > 2 weeks to complete a course of fractionated SRS 2.8 Resection is not performed (or cancelled) for any reason

*Abbreviation*: *SRS* stereotactic radiosurgery

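### For an unresected metastasis under 3 cm in the brainstem, the dose table, the brainstem limit and the deviation criteria cannot all be met

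*Protocol article*

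**What the plan says.** Five parts of the Protocol article meet here.

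- **Eligibility (Table 2).** Up to ten metastases are allowed and only one need be resectable. No exclusion depends on where a lesion lies.
- **Interventions.** "Patients treated on both arms will receive primary SRS for unresected brain metastases".
- **Table 3, intact metastases.** Dose depends on maximal diameter alone: "Lesions < 1.0 cm receive 22–24 Gy", "Lesions ≥1.0 to < 2.0 cm receive 20–22 Gy", and 18 to 20 Gy from 2.0 to under 3.0 cm. These three rows give no number of fractions, while the rows from 3 cm upward specify three or five. The table note adds: "The dose should be prescribed to the highest isodose line encompassing the CTV and be between the 50 and 90% of the maximum dose".
- **Radiotherapy, organs at risk.** The limits are given as "for Brainstem are Dmax ≤15 Gy in one fraction, ≤23.1 Gy in three fractions, and ≤ 31 Gy in five fractions".
- **Table 4, major deviations.** One is "2.2 Prescribed dose is ≤90% dose required by the study". Item 2.5 is triggered when "Maximum point dose to the brainstem is > 15 Gy for treatments delivered in one fraction".

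No text in the article makes an exception for brainstem lesions, says whether the target counts as brainstem, or ranks one rule above another.

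**The concern.** Each rule is clear alone. For a small unresected lesion in the brainstem, however, the Table 3 dose appears to exceed the organ limit, and a reduction large enough to respect the limit appears to be a major deviation. A site would then have to decide which rule to break.

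The first thing at stake is safety, because the rules give no single instruction for a critical organ. The second is consistency. If centres resolve the conflict differently, dose, local control and adverse radiation events will vary by centre for a reason the plan itself creates. Adverse radiation events are among the secondary endpoints named in the Abstract.

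**Working it through.** The brainstem limits are fixed constraints, so there is no derived figure to reproduce. The check asks whether any prescription satisfies every printed rule. The arithmetic only locates the clash and endorses no dose.

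**Inputs**
- Lowest Table 3 dose D for intact lesions: 22 Gy (under 1 cm), 20 Gy (1 to under 2 cm), 18 Gy (2 to under 3 cm). These are read as single-fraction. Using the bottom of each range is the lenient choice.
- Prescription isodose: 50 to 90% of the maximum (Table 3 note). The 90% line gives the lowest maximum.
- Brainstem limit: 15 Gy in one fraction (Radiotherapy; Table 4 item 2.5).
- Prescription at or below 90% of the required dose: major deviation 2.2.
- Coverage: 95% of the prescribed dose should encompass the CTV (Radiotherapy). From 90 to under 95% is minor deviation 1.1, and below 90% is major deviation 2.3.
- For intact lesions the CTV equals the GTV (Radiotherapy).

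**Step 1: the lesion counts as brainstem**

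Lowest maximum = D / 0.90. Highest prescription that meets the limit = 0.90 × 15 = 13.5 Gy. Prescription needed to avoid item 2.2: above 0.90 × D.

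| Size | D (Gy) | Lowest maximum (Gy) | 13.5 Gy as % of D | Must exceed (Gy) |
|---|---|---|---|---|
| < 1 cm | 22 | 24.4 | 61% | 19.8 |
| 1 to < 2 cm | 20 | 22.2 | 68% | 18.0 |
| 2 to < 3 cm | 18 | 20.0 | 75% | 16.2 |

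The ceiling of 13.5 Gy lies below the floor in every row, so there is no solution.

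**Step 2: the lesion is left out of the brainstem contour**

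Brainstem touching the lesion then receives about the dose at the CTV edge. Holding the prescription itself to 15 Gy gives 15/22 = 68%, 15/20 = 75% and 15/18 = 83% of D, all at or below the 90% threshold.

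The lowest edge dose without a major deviation combines a prescription just above 0.90 × D with 90% coverage, which is just above 0.81 × D:
- < 1 cm: 0.81 × 22 = 17.8 Gy, above 15.
- 1 to < 2 cm: 0.81 × 20 = 16.2 Gy, above 15.
- 2 to < 3 cm: 0.81 × 18 = 14.6 Gy, below 15.

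In the last row, coverage of 95% would give 0.95 × 16.2 = 15.4 Gy, which is over the limit. Coverage must therefore be no more than about 15 / 16.2 = 92.6%. That is minor deviation 1.1, at a prescription below the Table 3 range.

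**Step 3: lesions of 3 cm or more**

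Both rows offer 30 Gy in five fractions, against a limit of 31 Gy.
- Target excluded: 30 is below 31, so no reduction is needed.
- Target included: 30 / 0.90 = 33.3 Gy exceeds the limit. The limit allows 0.90 × 31 = 27.9 Gy (93% of 30) and item 2.2 requires more than 0.90 × 30 = 27.0 Gy. A prescription above 27.0 and up to 27.9 Gy triggers no listed dose deviation.

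The three-fraction schedules have no such window if the target is included. The ceiling is 0.90 × 23.1 = 20.8 Gy, against floors of 0.90 × 27 = 24.3 Gy and 0.90 × 24 = 21.6 Gy. The five-fraction alternative is open in both rows.

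**The case against.** The strongest reply is that this is a condensed article. The full protocol may hold a brainstem exception or a contouring rule, and Table 4 grades plans after the event rather than ordering anyone to exceed an organ limit. Both points are fair. They mean that the absence of a brainstem row or contour definition is not itself the finding. They do not remove the conflict, because the article prints the doses, limits and deviation thresholds as exact figures that cannot be satisfied together.

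A second reply is that the Abstract permits three or five fractions in either arm. The Background, however, ties fractionation to size, and Table 3 offers it only from 3 cm.

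A third is that the problem is rare and affects both arms alike. The documents give no frequency, and the intact-lesion doses do apply to both arms, so no bias in the randomized comparison is shown.

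Three stronger readings are tempting, and the documents do not support them:
- *Every eligible patient with a brainstem metastasis is a major deviation.* This is false at 3 cm or more. From 2 to under 3 cm the narrow combination in Step 2 also avoids one.
- *Any lowering of the dose is a major deviation.* Item 2.2 applies only at 90% of the required dose or less.
- *Such patients leave the per-protocol set.* Statistical analysis requires adherence to the assigned treatment and gives a cancelled resection as its example. It does not say that a major deviation excludes a patient. Removal is possible but is not a stated rule, and the intent-to-treat analysis keeps everyone.

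**Conclusion.** The point holds for unresected intact metastases under 3 cm lying in the brainstem. If the lesion counts as brainstem, the maximum is at least 20.0 to 24.4 Gy against 15 Gy, and respecting the limit means at most 61 to 75% of the lowest required dose. If the lesion is excluded, the conflict remains below 2 cm, and from 2 to under 3 cm the best available plan is still a minor deviation.

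This rests on three assumptions: the rows without a fraction count are single-fraction, the 90% isodose line is the most favourable case, and brainstem touching the lesion receives about the CTV edge dose. It does not depend on how common such lesions are. Each percentage point of enrolled patients with one is about 0.9 of the 88 planned, but the documents do not say how many points apply.

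The conflict should be resolved because it concerns a critical organ and the correction is small. It does not undermine the primary comparison.

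**What to change.** Reconcile Table 2, Table 3, the brainstem limits in the Radiotherapy section and Table 4 items 2.2 and 2.5 for brainstem lesions under 3 cm, so that one set of rules can be followed. State which rule takes precedence and whether the brainstem maximum includes the target. The choice of eligibility, dose and limit is for the sponsor and is not proposed here.

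Table 4 item 2.5 should be reconciled in the same pass for a separate mismatch: it prints "> 3.1 Gy for treatments delivered in three fractions", where the Radiotherapy section gives 23.1 Gy.

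The cost is a short clarification or amendment, and the wording change itself alters neither the sample size calculation nor the analysis. If the full protocol already settles the matter, citing that rule beside the tables would be enough. Any effect on accrual depends on the sponsor's choice.
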